**Figure 2 Fig2:**
[figure not shown]
SUMMIT study design and timeline.

For the RCT, all patients are screened for drug and alcohol use by clinic staff as part of usual care; eligible consenting patients (i.e., those with risky use or worse) are referred for further eligibility screening by the research staff, and eligible patients (*N* = 400) are invited to participate in the study. After consenting and completing the baseline interview at one of the study sites, patients are randomized to the ICC or SAU study condition. We use a concealed randomization protocol so neither patient nor research staff is aware of the randomization until after the baseline interview is completed when research staff open sequentially numbered envelopes that contain the randomization assignment. Assignments were made in advance by a statistician using R software. Patients complete a follow-up interview by telephone 6 months after the baseline interview.

The design is a variation of a “hybrid type 2” study, which Curran et al. [59] describe as the “simultaneous testing of a clinical intervention and an implementation intervention/strategy.” In this case, the organizational readiness intervention is the implementation intervention/strategy and the ICC service delivery intervention is the clinical intervention. The design, which incorporates implementation outcomes such as intention to adopt EBP as well as service system and patient outcomes, follows the recommendations for implementation research outcomes suggested by Proctor et al. [58].

### Study participants

#### Organizational readiness intervention

Organizational readiness intervention participants are full-time clinic administrators, medical and mental health providers, and other clinic staff, including medical assistants, discharge coordinators, and front desk and security staff who agree to participate in interviews, focus groups and/or surveys (*N* = 70).

#### Service delivery intervention

Service delivery intervention participants are full-time medical and mental health providers (not including residents) as well as patients who come to the clinic for a medical visit; the participants initially screen positive for risky (or worse) alcohol or opioid use using an adapted NIDA Quick Screen [60] and then meet all study eligibility criteria and consent to participate in the study (*N* = 400). To be eligible for the study, patients must be 18 years or older; meet the “Diagnostic and Statistical Manual of Mental Disorders, fourth edition (DSM IV)” criteria for abuse of or dependence on alcohol or opioids (heroin or prescription opioids) (assessed using the WHO ASSIST [61]); must not have marked functional impairment from bipolar disorder or schizophrenia; speak English or Spanish; and are not currently in treatment for SUD.

### Interventions

#### Organizational readiness intervention

To create organizational readiness to provide evidence-based treatment for OAUD, we employ multiple tools and activities known to facilitate adoption of EBP as follows: (1) engaging (and obtaining buy-in from) key administrators through regular administrator and board briefings about the proposed study and how to best prepare the organization to implement the ICC intervention and providers to adopt the EBP [29,62]; (2) convening an implementation team that includes key clinical leadership to develop the ICC service delivery intervention and EBP protocols that fit the clinic [29,63]; (3) selecting and training physician and therapist champions to serve as role models for adopting the EBPs [29]; (4) providing trainings for the staff and providers on the ICC intervention and evidence-based treatment for opioid and alcohol use disorders [64,65]; and (5) preparing the clinic environment to identify patients with SUD by instituting universal screening and brief intervention procedures. After preparing the organization, we then conduct the final part of the organizational readiness intervention—piloting the EBP and ICC protocols and making iterative adaptations using plan-do-study-act (PDSA) cycles [66,67]. PDSA cycles offer a structured approach to engaging staff in making iterative, feedback-based changes in service delivery [65,66].

#### Service delivery intervention

We use Wagner’s Chronic Care Model (CCM) [35] as the theoretical basis for the service delivery intervention (ICC). The ICC intervention is comprised of five components that have been shown to result in improved patient outcomes; each component supports the delivery of the planned care for opioid and alcohol use disorders: (1) redesigning the delivery system to support the delivery of the EBP and establishing a care coordinator; (2) modifying clinical information systems to provide alerts to indicate that patients have problematic substance use and developing a patient registry used by the care coordinators to monitor and track patients; (3) providing expert consultation to therapists for complex cases; (4) offering patients self-management tools; and (5) identifying and establishing linkages with community resources. These components are thought to lead to productive patient-provider interactions, which, in turn, lead to improved service system and patient outcomes. The ICC components are described in greater detail in Additional file 1.

### Outcomes, procedures, measures, and analysis plan

Next we describe our data collection procedures, measures, and analysis plans for the organizational readiness and service delivery interventions.

#### Organizational readiness intervention

##### Procedures

We use qualitative and quantitative methods to study our organizational readiness outcomes as follows: 1) *Provider focus groups and semi-structured interviews*. We conduct focus groups with medical and mental health providers and one-on-one interviews with key administrators to inform the development of our intervention and EBP protocols and to understand perceptions of acceptability, appropriateness, feasibility, and intention to adopt the ICC and EBP protocols. For both the focus groups and the interviews, we follow a semi-structured protocol guide that asks “grand tour” questions related to each domain (i.e., general thoughts about ICC and the EBP), and includes specific probes for more detailed responses. 2) *Provider Surveys*. We also conduct surveys in years 1–5 with all the staff and providers to assess changes in organizational readiness outcomes throughout the study. The survey includes validated measures as well as “home-grown” items about specific activities, such as whether providers prescribed a medication and any barriers to doing so. Surveys are web-based, or, for providers with less access to email, through in-person, paper and pencil surveys.

##### Measures

We measure organizational readiness using outcomes for implementation research recommended by Proctor et al. (2011) [58]. We will evaluate the following outcomes specifically related to our organizational readiness intervention: (1) *Acceptability*. Acceptability refers to satisfaction among implementation stakeholders with the complexity of an EBP or new practice (such as the ICC intervention) and relative advantage over current practices [58]. To assess acceptability we adapted items for the staff survey from Moore and Benbasat’s [68] validated instrument which maps onto parallel elements of Roger’s elements of successful diffusion (i.e., complexity, relative ease of use) [69]. An example of these items is: *Prescribing extended-release injectable naltrexone for patients with alcohol use disorders at this clinic would be relatively easy to do*. We also include locally developed items in the survey to capture barriers to use as well as items from the National Center for Addiction and Substance Abuse’s (CASA) National Survey of Primary Care Physicians and Patients on Substance Abuse [70] that capture providers’ opinions about the effectiveness of OAUD EBP, as well whether providers find it difficult to discuss OAUD with their patients. We ask specific questions about acceptability in the focus groups and interviews, such as: *How easy or difficult would it be for providers to prescribe and administer extended-release injectable naltrexone? What are some of the barriers? What changes would have to be made to make it more acceptable?* (2) *Appropriateness*. This refers to the “perceived fit, relevance, or compatibility” [58] of the EBP and ICC intervention in the clinic. We have adapted items from Moore and Benbasat [68] that measure compatibility of EBP and the ICC intervention with the clinic and with current work style (also an element of Roger’s diffusion theory) [69]. This includes items such as: *I think the ICC intervention will fit with the way I like to work*. We also include items from the “Substance Abuse Attitudes Survey (SAAS)” to measure changes in provider attitudes about people with substance abuse disorders [71]. The focus groups and interviews also capture reasons why the EBP or ICC intervention may or may not be perceived as compatible with work style and with other approaches to managing patients with OAUD or introducing new practices into the clinic. (3) *Intent to adopt the EBP*. We assess intention to adopt EBP in several ways. First, we incorporate into the survey the *EBP Attitude Scale (EBPAS)*. The EBPAS is a brief (15-item), valid, reliable measure that assesses general attitudes toward adoption of new clinical practices [72]. Next, we use items from Moore and Bensabet’s scale that measure elements associated with successful adoption of new EBP [68]. To measure intention or willingness to adopt, we use the “demonstrability” scale, which asks questions such as “*I believe I can communicate to others the consequences of using extended release injectable naltrexone*.” Finally, we ask questions in the focus groups and interviews about intent to adopt. (4) *Feasibility*. Feasibility is the actual fit, utility, and suitability of a program within an organization: the practicability [58]. We assess feasibility retrospectively by asking participants in focus groups and interviews whether the EBP and ICC intervention were successfully implemented and whether poor resources, training, or other barriers impeded use. We also ask about feasibility in the provider survey using items from CASA’s National Survey of Primary Care Physicians and Patients on Substance Abuse that capture how prepared providers feel they are to treat patients with SUD [70]. (5) *Adapted EBP and intervention protocols*. Our final measure of readiness is finalized, adapted protocols for each of the three EBP and the ICC service delivery intervention, which describe how the EBP fit into the clinic workflow. Adapted, finalized protocols are key to ensuring that staff can visualize how the EBP and ICC intervention will be implemented.

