### Conceptual framework

In our conceptual framework, illustrated in Figure 1, the organizational readiness intervention increases provider readiness to use each of the EBP for OAUD (the two medications and the MI-based behavioral therapy) as well as readiness to adopt ICC (the service delivery intervention) to deliver the three EBP. The organizational readiness intervention consists of well-studied “implementation” tools, designed to increase the readiness of an organization to implement and deliver new practices. Our measures of organizational readiness are provider acceptability of the EBP, provider perceptions of EBP appropriateness and feasibility, and provider intention to adopt each EBP. In addition, because an aspect of organizational readiness is the ability of providers to visualize how the new practices can be adopted and integrated into the existing workflow [33], a final measure of readiness is the development of locally tailored EBP protocols and an ICC protocol that shows how the EBP will fit into clinic workflow.

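### The only treatment-specific survey scale labelled as intention to adopt appears to measure ability to explain the treatment, so a rise on it should not be reported as increased intention

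*Protocol article*

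**What the plan says.** The Conceptual framework section of the protocol article lists "provider intention to adopt each EBP" among the measures of organizational readiness. The Measures section for the organizational readiness intervention then sets out how it is assessed: "We assess intention to adopt EBP in several ways". Four routes follow.

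- The EBPAS, described thus: "The EBPAS is a brief (15-item), valid, reliable measure that assesses general attitudes toward adoption of new clinical practices".
- Items from an adapted innovation-perception instrument "that measure elements associated with successful adoption of new EBP".
- A scale assigned to the construct by name: "To measure intention or willingness to adopt, we use the “demonstrability” scale". Its single example item is "I believe I can communicate to others the consequences of using extended release injectable naltrexone".
- Questions about intent in the focus groups and interviews.

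The Interventions section includes, as one component of the readiness intervention, "providing trainings for the staff and providers on the ICC intervention and evidence-based treatment for opioid and alcohol use disorders". The Analysis plan for that intervention compares survey items before and after by one-way repeated measures ANOVA. It subjects the interview and focus group data to content analysis for facilitators and barriers. The Discussion says the readiness outcomes will show whether the intervention improves intention to adopt.

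**The concern.** The name given to the scale and the content of its example item do not match. Being able to tell others what a drug does is a matter of knowledge and confidence; intending to use it is a matter of willingness. The two can part company in either direction. A prescriber may explain the consequences well and have decided not to prescribe, and another may be ready to prescribe but feel unable to explain the drug to colleagues.

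This matters more here than in an ordinary survey because the intervention under test teaches the very thing the item asks about. If training improves understanding and leaves willingness where it was, the score rises and, under the label the article gives it, the rise would be reported as greater intention to adopt. A stated conclusion of the readiness part of the study would then rest on something close to a check that training was absorbed.

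**Working it through.** No arithmetic applies. The question is whether the content of each measure fits the construct it is meant to represent, so the check sets each route beside the target, which is intention to adopt each individual EBP.

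| Route (Measures section) | Content as described | Specific to an EBP? | Asks about intention? | Planned analysis |
|---|---|---|---|---|
| EBPAS | General attitude to new practices | No | No, general attitude | Pre-post ANOVA |
| Adapted perception items | Correlates of successful adoption | Not stated | No, correlates | Pre-post ANOVA |
| Demonstrability scale | Ability to communicate consequences of use (one item shown) | Yes | Labelled so; the item does not | Pre-post ANOVA |
| Focus groups and interviews | Direct questions on intent | Can be | Yes | Content analysis |

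The second and third survey routes may come from the same instrument; the table does not depend on this.

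Step 1. Of the routes that enter the pre-post ANOVA, none is described as asking about intention to adopt a specific EBP. The route that asks about intent directly is qualitative, and its planned analysis looks for facilitators and barriers rather than quantified change.

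Step 2. The mismatch is particular to this scale. In the same section, the example item for acceptability asks how easy prescribing would be, and the example for appropriateness asks about fit with the respondent's way of working. Both suit their labels.

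Step 3. The readiness comparison is before versus after, with no comparison group. An observed change in demonstrability is the sum of any change in understanding, any change in willingness that the items happen to pick up, and any change over time from other causes. With one score and no control, those parts cannot be told apart, whatever the sample size. The document gives no figure for how far training moves the scale, so no numerical size can be attached to the distortion.

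Step 4. The reach of the problem is limited. Intention is one of five readiness measures; the others are acceptability, appropriateness, feasibility and the adapted protocols. Actual adoption is measured separately under Service system measures, from prescription and therapy records and provider self-report.

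**The case against.** The strongest reply is that the article assesses intention by several routes and that demonstrability is only one of them. This stands. A reader might infer that intention is never measured, and the document does not support that: general attitudes toward adoption are surveyed, and intent is asked about directly in focus groups and interviews.

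Second, a whole scale should not be judged on one item from a condensed article. This stands in part. The remaining items are not shown, the survey also contains locally developed items that are not listed in full, and the source instrument is not available here. The finding is therefore limited to what the article describes. Even so, the article itself chose this item to illustrate intention, and the item does not do so.

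Third, the effect of training is inferred. It is tempting to say that training alone raises the score, or that the whole observed change could be spurious. Nothing in the document shows either, and training is also meant to build readiness, so a rise that follows training is not false in itself. What remains is that the design cannot say which kind of rise it has seen.

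Fourth, because the participants include "medical assistants, discharge coordinators, and front desk and security staff", a reader might infer that the medication items are pooled over staff who could not prescribe. The article says the survey goes to all staff and providers. It does not say which items each role receives or how roles are combined, so that inference is not part of the finding.

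Last, the harm is contained because adoption is measured directly. This is correct: a mislabelled scale cannot create a false adoption result.

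**Conclusion.** The concern holds in a limited form. The only EBP-specific survey scale that the article labels as intention or willingness appears, on its one published item, to capture perceived ability to explain the EBP. No other survey measure described captures EBP-specific intention. A pre-post rise on demonstrability therefore does not support the statement that intention to adopt increased.

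The conclusion rests on two assumptions: that the example item is representative of the scale, and that the unlisted survey items contain no direct question on intention for each EBP. If either is wrong, the point weakens accordingly. It affects the interpretation of one readiness measure out of five and leaves the randomized patient comparison untouched.

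**What to change.** - Report demonstrability under its own name, as perceived ability to explain the EBP, and do not cite a rise on it as increased intention.
- Describe the EBPAS result as general attitude toward new practices.
- Base any statement about intention to adopt a particular EBP on the focus group and interview questions.
- Optionally, add one direct intention item per EBP (three in all) to the remaining annual surveys and summarise it descriptively among the staff who can deliver that EBP.

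The first three changes need no new data. Their price is that the quantitative claim of a rise in EBP-specific intention from year 1 is given up. The optional items would not restore it, because they have no year-1 value. They would also rest on subgroups of the 70 staff whose sizes the article does not give and which are bound to be small.

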
##### Analysis plan

The semi-structured interview and focus group data will be analyzed to identify key facilitators and barriers to implementation using classic content analyses. Our quantitative analysis of survey items will consist of pre-post, one-way repeated measures ANOVA comparisons of survey responses between pre- and all post-intervention periods.

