### Study design

The study is designed to test the combined effect of both an organizational readiness intervention (which includes a 1-year organizational preparation period and an 8-month pilot of the ICC condition study) and a service delivery intervention (see Figure 2). We examine the effects of the interventions on organizational readiness, service system, and patient outcomes, all of which are believed to be important in understanding the uptake of new practices [58]. To test the unique effects of the organizational readiness intervention on provider outcomes, we use a pre-post-intervention design and measure these outcomes at the beginning of the study and then again at the end of year 1. At the end of year 1, we implement an eight-month pilot test of ICC. During the pilot test, providers gain experience with the protocols, and the protocols are iteratively adapted and refined based on provider feedback. Because we hypothesize that readiness outcomes may continue to improve as providers gain experience with ICC and the three treatments, we continue to measure organizational readiness outcomes annually at years 2–5. Thus, changes in outcomes between year 1 and years 2–5 reflect the combined effect of both the organizational readiness intervention and ICC on provider outcomes. To test the effects of the interventions on service system and patient-level outcomes, we are conducting an RCT to compare the effects of ICC with SAU. Service-system outcomes are patient-centered collaborative care, utilization of SUD treatment, patient utilization of health care services, provider adoption of EBP, and sustainability of EBP. Patient-level outcomes include substance use, consequences of use, physical and mental health functioning, and patient satisfaction with SUD care.

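### The repeated-measures ANOVA fixed for the staff surveys drops leavers, skippers and joiners, and the year-1 readiness contrast measures only the preparation part of the intervention it is said to test

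*Protocol article*

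**What the plan says.** On data collection, the Procedures for the organizational readiness intervention state: "We also conduct surveys in years 1–5 with all the staff and providers". Study participants gives a staff sample of 70, counted across interviews, focus groups and surveys together. On timing, the Study design section says the investigators "measure these outcomes at the beginning of the study and then again at the end of year 1", and then that "we continue to measure organizational readiness outcomes annually at years 2–5". Read with Procedures this is five waves; read on its own it can be six.

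On analysis, the readiness Analysis plan says: "Our quantitative analysis of survey items will consist of pre-post, one-way repeated measures ANOVA comparisons", made as "comparisons of survey responses between pre- and all post-intervention periods". No other quantitative method is named for these surveys. The service delivery Analysis plan names the same ANOVA for provider survey items. For patients, that section provides response weights for attrition and hierarchical models; for staff it provides neither.

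On the readiness contrast, the Study design section uses the start and end of year 1 "To test the unique effects of the organizational readiness intervention on provider outcomes". The same section counts an eight-month pilot as part of that intervention and says: "At the end of year 1, we implement an eight-month pilot test of ICC". The Interventions section also describes the pilot as the last part of the readiness intervention.

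**The concern.** A staff roster that includes medical assistants, front desk and security staff can be expected to change over five years. A classical one-way repeated-measures ANOVA needs a complete row for each person across the waves it compares. It has no place for someone who leaves after year 2, misses the year 3 survey, or is hired in year 2 and has no pre measurement. Their answers are collected and then not used.

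Two things are at stake. The first is precision: with at most 70 staff to begin with, each loss counts. The second is validity: if leaving or not answering is related to readiness, the staff who remain may not show the change that the whole staff would show.

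The second issue concerns labelling. A contrast that ends before the pilot begins cannot show the effect of an intervention that includes the pilot. A reader would credit, or deny, the full readiness intervention on the evidence of its first part.

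**Working it through.** The article states no power, detectable difference, response rate or turnover for the staff surveys, so there is no planned figure to reproduce. What follows is a range under stated assumptions.

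**Inputs.** From the article: 70 staff; five waves (Procedures) or six (Study design). Assumed: all 70 answer the first wave; a share q of those still answering also answers the next wave, with q from 0.95 to 0.70; correlation of 0.5 between two waves within a person.

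**Staff with every wave.** Five waves: 70 × q^4. Six waves: 70 × q^5.

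| Lost per wave | q | Five waves | Six waves |
|---|---|---|---|
| 5% | 0.95 | 57.0 | 54.2 |
| 10% | 0.90 | 45.9 | 41.3 |
| 15% | 0.85 | 36.5 | 31.1 |
| 20% | 0.80 | 28.7 | 22.9 |
| 30% | 0.70 | 16.8 | 11.8 |

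If nobody leaves but each person answers each wave independently with probability 0.9, 0.8 or 0.7, then 70 × p^5 gives 41.3, 22.9 or 11.8 with all five.

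**If pre is compared with each post wave separately.** The number used is 70 × q^k for the k-th later wave. At q = 0.95 this is 66.5, 63.2, 60.0 and 57.0; at q = 0.70 it is 49.0, 34.3, 24.0 and 16.8. The early comparisons keep far more staff. When loss is by leaving, the last comparison keeps no more than the all-wave analysis. With independent skipping the gain is larger: at p = 0.8, 70 × 0.8² = 44.8 instead of 22.9. Joiners without a pre measurement are excluded under either reading.

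**Precision.** Detectable within-person difference at 80% power and two-sided 5%, in SD units: (1.96 + 0.84) × √(2(1 − 0.5)/n).

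- n = 70: 0.33
- n = 57: 0.37
- n = 46: 0.41
- n = 29: 0.52
- n = 17: 0.68

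**Direction of bias.** An illustrative simulation used 70 staff, five waves, correlation 0.5, a true change of zero, and a chance of staying that rose with the previous score (the strength of this was assumed), over 150 replicates. About 28 staff completed all waves. They started 0.39 SD above the full staff, but their mean change from first to last wave was −0.07 SD, against 0.00 SD from a mixed model on all responses. The SD of a change is √(2(1 − 0.5)) = 1, so the simulation error of that mean is roughly 1/√28/√150 = 0.015. The small negative value is therefore not noise: staff selected for high earlier scores tend to fall back. Other patterns of leaving would give other results.

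**The year-1 contrast.** Set side by side:

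- Study design: the readiness intervention is a one-year preparation period plus an eight-month pilot.
- Interventions: the pilot is its final part.
- Study design: its unique effects are tested from the start to the end of year 1.
- Study design: the pilot starts at the end of year 1.

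The measurement window closes when the pilot opens. This step needs no assumption.

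**The case against.** Much can be said for the plan as written.

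- **A condensed article.** Handling of missed waves, sphericity corrections and rules for joiners and leavers may sit in a full plan that is not shown. Their absence is therefore not the point. What stands is that the article positively fixes a method with this property, as the only quantitative method for the staff surveys.
- **The wording is open.** It speaks of comparisons in the plural and does not say that one ANOVA spans all waves. That stands, and it reduces the loss for the early comparisons.
- **A small group of stayers.** A reader might infer that the result rests on a small, self-selected group. The article does not support that as fact: the range runs from 57 to 12 of 70, and the 70 is not stated as a survey denominator. Readiness is also assessed by focus groups, interviews and finalized protocols.
- **Most surveys discarded.** This fails at 10% loss with full response otherwise: 46 × 5 = 230 of at most 70 × 5 = 350 are kept.
- **Inflated gains.** A reader might expect favourable stayers to exaggerate improvement. The analysis is within person, so a stable difference in favourability cancels. Inflation needs selection on change, which is not shown, and the simulation went slightly the other way.
- **Wrong contrast.** Pre versus all post might seem not to be what the study set out to test. It is: the Background section hypothesizes improvement from year 1 to years 2–5, and the Study design section says this reflects both interventions together.
- **The remedy has a weakness.** Joiners may have missed the year-1 preparation, so including them alters the question. This stands and shapes the sensitivity analyses below.

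**Conclusion.** The point holds as a conditional weakness in the named method and as a definite labelling error in one contrast.

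The ANOVA, in its classical form, loses every staff member without data at each wave compared and every joiner without a pre measurement. If all 70 answer the first wave and 5% to 30% are lost per wave, 57 to 17 have all five waves, or 54 to 12 of six. With a correlation of 0.5, the five-wave loss raises the detectable within-person change from 0.33 SD at n = 70 to between 0.37 and 0.68 SD. The actual loss is unknown. Selection bias is a risk whose size and direction depend on why staff leave or do not answer. The same applies to the provider survey outcomes in the service delivery analysis plan.

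The start-versus-end-of-year-1 contrast measures the preparation part only and cannot carry the label of the whole readiness intervention.

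The analysis should be changed. Neither issue touches the randomized patient comparison.

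**What to change.** Replace the ANOVA for staff survey outcomes, in both analysis plans, with a linear mixed model: wave as a categorical fixed effect, a random intercept for each staff member, adjustment for site and role, and all linked responses included. The article already names suitable software for the patient outcomes.

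Contrasts to state in advance:

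- Keep year 1 versus years 2–5, as hypothesized in the Background section, and say which year-1 measurement is the reference.
- Relabel start versus end of year 1 as preparation only.
- Label later contrasts as readiness plus pilot/ICC exposure combined. A wave after the pilot should not be called the readiness intervention alone, because the pilot is itself a pilot of ICC.

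Report the number of respondents at each wave. As sensitivity analyses, restrict to staff with a pre measurement, since joiners may not have been exposed to year-1 preparation, and to all-wave completers.

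The cost is slightly more modelling on the same data. Staff identifiers must link across waves, which should be confirmed. The mixed model does not remove bias if leaving depends on readiness that was never observed, so the counts and sensitivity analyses remain necessary.
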